## Methods

### Study design

The study is designed as a controlled parallel group study with two arms, with the control group of parents receiving the existing publicly available postnatal care services in the 10 municipalities, i.e. Care As Usual (CAU), and the intervention group of parents receiving the Understanding Your Baby (UYB) integrated in to the existing publicly available postnatal care services (i.e. CAU). Both groups come from the same 10 municipalities. The CAU group is included in the project’s first phase and when data collection for this group is finished, all health visitors in the 10 municipalities are trained in delivering the UYB intervention. When the health visitors have finished their training, the UYB group is included in the project’s second phase.

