### The study interventions

During the project’s first phase, the participants will receive the existing publicly available postnatal care services (CAU) in the 10 municipalities and these may vary as described in Table 2. In the project’s second phase, the participants will receive the UYB intervention integrated into the existing publicly available postnatal care services in the 10 municipalities. The dose of UYB will therefore vary according to the variation in the existing postnatal care services (Table 2).

**Table 2 Tab2:** Information on visits from the health visitor and ADBB observations in the 10 municipalities

	Number of visits from the health visitor 0–12 months postpartum	Infant's age (months) when ADBB is conducted	Number of ADBB observations in total	ADBB observation 2–3 months	ADBB observation 4–6 months	ADBB observation 8–10 months
*Municipality*						
Aalborg	5	2, 4–6, 8–10	3	X	X	X
Frederiksberg	5	4, 8	2		X	X
Holbæk	6	2, 4, 8	3	X	X	X
Hvidovre	7	2, 8–10	2	X		X
Høje-Taastrup	6	2–3, 4–6	3	X	X	
Køge	5	2–3, 4–6, 9–10	3	X	X	X
Lolland	7	2, 4, 6, 8	4	X	X	X
Middelfart	6	2, 4, 8	3	X	X	X
Nyborg	5	2, 8–10	2	X		X
Næstved	7	4	1		X	

ADBB = Alarm Distress Baby Scale

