### Statistical methods

The analyses of both primary and secondary outcomes will be conducted under the intention to treat principle where the participants are analysed according to their control CAU/intervention UYB status. However, as a secondary analysis, we will also conduct analyses where the actual intervention participation is taken into account (i.e. whether the families in the UYB group have been given the intervention by the health visitors). Thus, we will perform a contamination adjusted intention to treat analysis [61] which compliments the intention-to-treat approach by producing a better estimate of the effect of the UYB intervention.

The primary endpoint is PSOC at 11 months postpartum. The level of significance will be 5%, two-tailed [62]. The primary comparison of UYB and CAU interventions is analysed using linear mixed models with the health visitor as the second order variable. This is done to account for the correlation induced by the same health visitor conducting the CAU and UYB intervention for multiple families. We will control for maternal educational level in years, maternal level of depressive symptoms, and maternal age in years.

Secondary outcomes will be analysed in the same way as the primary outcome. Binary and categorical outcomes will be analysed with mixed logistic and multinomial logistic regressions, respectively, and continuous outcomes with mixed linear regression analyses. For outcomes where we are interested in the individual variance across time points, generalized estimating equations will be employed. All the analyses will be adjusted for the abovementioned covariates. As multiple tests will be conducted, we will both assess significance using the 5% significance level and adjust for multiple testing using the Bonferroni-Holm method [63].

For the tertiary outcome, we investigate whether some subpopulations benefit more from the UYB intervention. These subpopulations will be defined as disadvantaged families (e.g. based on background information such as employment status, income, etc.) versus advantageous families as well as families with a more intensive UYB implementation. In practice, we will test for significant subpopulations-group status interaction effects using linear moderation analyses (as otherwise described above).

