### Dates defining periods of recruitment and follow-up

The project’s first phase, i.e. recruitment of the CAU group, began May 15th, 2019 and ended February 29th, 2020. This group includes parents and their infants born from April 1st until September 30th, 2019 in the 10 municipalities. In August 2020, the health visitors began training in the UYB-intervention. However, due to COVID-19, the training of the health visitors in three of the 10 municipalities had to be postponed and was finished by March 2021. In seven municipalities, the project’s second phase, i.e. the recruitment of the UYB group, will take place in the period from February 15th until November 30th, 2021. This group includes parents and infants born from January 1st until June 30th, 2021. In the three municipalities where the UYB training was delayed, the participant recruitment will take place in the period from May 15th, 2021 until February 28th, 2022. This group includes parents and infants born from April 1st, 2021 and until September 30th, 2021. Data collection will go on until December 2022.

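### UYB start window and dose are set by municipality, but the primary model has no municipality term; its standard error is too small if the change between phases differs by municipality

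*Protocol article*

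**What the plan says.** Under Statistical methods, the protocol article names the primary analysis as "linear mixed models with the health visitor as the second order variable" and gives the reason: "This is done to account for the correlation induced by the same health visitor conducting the CAU and UYB intervention for multiple families". The covariates are listed in full: "We will control for maternal educational level in years, maternal level of depressive symptoms, and maternal age in years". Secondary outcomes are to be analysed in the same way.

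Three other sections bear on the point.

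- **Study design.** "Both groups come from the same 10 municipalities", and "when data collection for this group is finished, all health visitors in the 10 municipalities are trained in delivering the UYB intervention". Within each municipality, group therefore equals calendar phase.
- **The study interventions.** "The dose of UYB will therefore vary according to the variation in the existing postnatal care services". Table 2 lists from one ADBB observation (Næstved) to four (Lolland).
- **Dates defining periods of recruitment and follow-up.** "the training of the health visitors in three of the 10 municipalities had to be postponed and was finished by March 2021". CAU infants were born April to September 2019 everywhere. UYB infants are born January to June 2021 in seven municipalities and April to September 2021 in the other three.

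**The concern.** The clustering argument stops at the health visitor, while the switch from CAU to UYB is organised one level higher. A visitor intercept moves a visitor's CAU and UYB families up or down together. It cannot represent a change between phases that is larger in one municipality than in another.

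The article gives reasons why such a difference is possible. Adding 11 months to the birth windows puts the primary endpoint at about March to August 2020 for CAU, December 2021 to May 2022 for UYB in seven municipalities, and March to August 2022 in three. The season therefore changes between phases in seven municipalities and stays the same in three. The Discussion also concedes that the pandemic may have affected participants differently between and within groups, and may have affected delivery.

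The size of the primary test is at stake, and to a lesser degree bias from a changed recruitment mix.

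**Working it through.** **The plan's own figures.** The dropout step reproduces: 690 / 0.75 = 920. The 690 cannot be checked. Without covariates, d = 0.2 with 80% power and two-sided 5% needs 786 in total; 690 would follow if the covariates explained 1 − 690/786 = 12% of the variance. The article prints neither that share nor an intraclass correlation, and mentions no municipality term in the power model.

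**Inputs.** N = 690 analysed (Sample size); about 230 health visitors (Study setting); births per municipality in 2020 (Table 1), total 7,781. With w = share of births, Σw² = 0.166, equivalent to about 6.0 equal municipalities. Assumed: ρ, the municipality-by-phase variance as a share of total variance, at 0, 0.5% and 1%.

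**Formula.** The true variance of the group difference is (1 − ρ)·4/N + 2ρ·Σw², against 4/N in the planned model. The ratio is

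DE = 1 − ρ + ρ·(N/2)·Σw².

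The type I error is 2·[1 − Φ(1.96/√DE)].

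| ρ | DE, sizes by births | Type I error | DE, equal sizes | Type I error |
|---|---|---|---|---|
| 0 | 1.00 | 5.0% | 1.00 | 5.0% |
| 0.5% | 0.995 + 0.005 × 345 × 0.166 = 1.28 | 8.3% | 1.17 | 7.0% |
| 1% | 0.99 + 0.01 × 345 × 0.166 = 1.56 | 11.7% | 1.34 | 9.0% |

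**Check by simulation.** 2,000 runs per setting; 690 families; about 230 visitors nested in 10 municipalities sized by births; REML fit with a visitor intercept only; visitor variance assumed at 3%. The Monte Carlo standard error near 5% is √(0.05 × 0.95/2000) = 0.5 percentage points.

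- *Stable municipality differences only*, at 0%, 2% or 5% of variance: true SE / reported SE = 0.99 throughout; type I error 4.6%, 5.0%, 4.9%.
- *Shift in mix*: 5% municipality variance, with the largest municipality weighted 1.5-fold in the UYB phase: SE ratio 1.02, type I error 6.0%.
- *Municipality-by-phase variance* of 0.25%, 0.5%, 1%, 2%: SE ratio 1.06, 1.12, 1.26, 1.46; type I error 6%, 8%, 12%, 19%.

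The last set agrees with the formula: √1.28 = 1.13 and √1.56 = 1.25.

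**Why the visitor intercept absorbs little of a mix shift.** There are 690/230 = 3 mothers per visitor, or 1.5 per phase. If visitor and municipality together carry 8% of the variance (3% + 5%, as in the mix-shift setting), the shrinkage weight is 3 × 0.08/(1 + 2 × 0.08) = 0.21. Only about a fifth of a between-visitor difference is removed.

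**Interval width once the variation is allowed for.** With t on 9 df, the width relative to the planned interval is √DE × 2.262/1.960. That is 1.31 at ρ = 0.5% and 1.44 at ρ = 1%. At ρ = 0 the t reference alone would add about 15%.

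**The case against.** The strongest reply is that municipality is crossed with group. A reader might infer from the wide spread in Table 1 that omitting municipality makes the standard error too small in any case. The design does not support that: stable differences largely cancel, and the simulation shows type I error near 5% even at 5% municipality variance. This reply stands, and it makes the point conditional. The Table 1 spread in education is also partly covered, because each mother's education is already a covariate. No change in mix is documented, and the mix-shift setting gave only 6.0%.

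The evidence for a differing change is indirect. The article describes a national lockdown and restrictions that varied over time; it does not say that restrictions differed locally. It documents two UYB birth windows, not ten. Differing dose does not raise type I error if UYB has no effect anywhere; it matters only once UYB works. Even then, for a target confined to these 10 municipalities, treating their effects as random is a choice. Implementation intensity is already a planned moderator. All this stands. It argues for keeping the random term out of the primary analysis, but does not show that ρ is zero.

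It may also be said that the full analysis plan could add municipality. But the article states the model, its covariates and its reason for clustering, so the gap can fairly be raised.

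**Conclusion.** The point holds conditionally. The stated model omits the level at which the start window and dose of UYB are set. The consequence for the standard error depends on a variance that the documents do not give: type I error is about 5% if the change between phases is the same everywhere, and about 8% or 12% if municipality-by-phase variance is 0.5% or 1% of the total. These figures assume 690 mothers and participation in proportion to births; equal-sized municipalities give 7% and 9%. The mix-shift problem is smaller, but cheap to close.

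Two further inferences should be resisted.

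- A reader might take the inflation as an equally large loss of power in the planned test. If 690 gives exactly 80%, that test would reject with probability Φ(0.84/√DE), about 77% or 75%. Its main fault would be false positives. A larger loss belongs to a corrected test.
- A reader might extend the criticism to the plan that "For outcomes where we are interested in the individual variance across time points, generalized estimating equations will be employed", as if GEE had to ignore either the parent or the visitor. Clustering on the visitor with robust standard errors also covers parents nested within visitors, and the primary endpoint is a single time point. No finding is made there.

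**What to change.** 1. Add municipality as a fixed effect (10 levels, 9 df) to the primary and all secondary models. It protects against a shift in mix between the phases. It does not by itself repair the standard error if the change differs by municipality.
2. Prespecify one sensitivity analysis of the primary outcome, reported beside the main result. Use either a random group-by-municipality term with small-sample degrees of freedom (for example Kenward–Roger), or municipality-robust standard errors with a small-sample correction.

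The first step costs 9 degrees of freedom out of several hundred and needs no new data, since residence in a participating municipality is an inclusion criterion. The second gives a clearly wider interval, about 30% to 45% at the assumed 0.5% and 1% with about 9 df. That is a reason to keep it as a sensitivity analysis, since making it primary would be a real trade-off.

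Neither step separates UYB from calendar changes shared by all 10 municipalities, and the report should say so.

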### Purpose of the study

The purpose of the current study is to evaluate the efficacy of the newly developed UYB program in 10 Danish municipalities. More specifically, the aim of the study is to test whether Care As Usual (CAU) including the UYB program in comparison to CAU alone will lead to:Improved maternal competence (primary outcome)Improved paternal competence (secondary outcome)Improved parental mentalizing, i.e. reflective functioning and mind-mindedness (secondary outcome)Reduced parental stress (secondary outcome)Improved infant socioemotional development (secondary outcome)Reduced infant social withdrawal (secondary outcome)Reduced parental media use and infant screen time (secondary outcome)Increased information about infant socioemotional development (secondary outcome)Heterogeneity of effects across family types with more disadvantaged families and families met with more intensive UYB implementation gaining more from participation in the intervention (tertiary outcome)

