*Parenting stress* will be measured using the Parenting Stress Index, Fourth Edition – short form (PSI-4-SF; [57]), a 36-item questionnaire measuring stress in relation to being a parent. Each item is rated on a 5-point Likert type scale from “Strongly disagree” (= 1) to “Strongly agree” (= 5). The PSI-SF provides a total score and three subscales: (a) Parental distress, measuring stress related to the parent’s experience of parenting and/or his or her parenting abilities (e.g. “I feel trapped by my responsibilities as a parent”), (b) Parent–child dysfunctional interaction, measuring stress related to the parent’s experience of interactions with his or her child (e.g. “I expected to have closer and warmer feelings for my child than I do, and this bothers me”), and (c) Difficult child, measuring stress related to the parent’s experience of his or her child’s characteristic (e.g. “My child makes more demands on me than most children”). Parenting stress is measured at 4 and 11 months.

*Infant socioemotional development* will be measured using the Ages & Stages Questionnaires®: Social-Emotional, Second Edition (ASQ:SE-2; [58]). The ASQ:SE-2 questionnaire for children aged 9 to 14 months contains 27 items assessing the presence of different socioemotional behaviors (e.g. “Does your baby smile at you and other family members?”). There are three choices for each item: “Most of the time” (= 0), “Sometimes” (= 5), and “Rarely or never” (= 10). In addition, the parent can check a “concern” option for each item, which adds 5 points to the score for that item. Items are summed to a total score with higher values reflecting less optimal socioemotional development. Empirically derived cutoffs are available to determine whether the child’s socioemotional development appears to be on schedule, in the monitor zone, or in need for further evaluation [58]. Infant socioemotional development is measured at 11 months.

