*Infant social withdrawal* will be measured using the Alarm Distress Baby Scale (ADBB; [15]). The ADBB is an observer-rated screening tool consisting of eight items: Facial expressions, Eye contact, General level of activity, Self-stimulating gestures, Vocalizations, Briskness of response to stimulation, Relationship, and Attraction. Each item is rated on a 5-point scale from “Absolutely normal” (= 0) to “Very obvious abnormal behavior” (= 4). Items are summed to a total score with higher scores indicating more social withdrawal. A cutoff of ≥ 5 may be used to identify infants showing clinical levels of social withdrawal [15, 23–25]. The ADBB data will be obtained from the health visitors’ register and will be based on the ADBB observations performed by the health visitors at the home visits (see Table 2).

*Parental media use and infant screen time* will be measured using a short questionnaire developed by the authors focusing on the use of different types of screens (television, tablets, smartphones, etc.) in the families (Additional file 1). The questions address the parent’s screen time during the infant’s awake time (total minutes per day), the infant’s screen time (total minutes per day), and the parent’s perception of technoference in the parent–child relationship (number of disturbances per day). Media use is measured at 2, 4, 7, and 11 months.

*Information about infant development* is assessed at 11 months using a short questionnaire developed by the authors (Additional file 2). Parents are asked to what degree they have been informed about each of the following topics by their health visitor during their infant’s first year: (a) My child’s physical development, (b) My child’s nutrition and sleep, (c) My child’s emotional development, (d) How I manage my child’s emotions, (e) My child’s social competences and development, and (f) How I support my child’s social development. In this study, we are interested in whether parents have received more information about the last four topics.﻿ 

Table 3 shows an overview of all the questionnaires that are completed by the parents at the different measurement points.

**Table 3 Tab3:** Points of measurements of control variables, primary and secondary outcomes

Measures	T1 (2 months)	T2 (4 months)	T3 (7 months)	T4 (11 months)	Obtained from the health visitors’ register
*CAU and UYB*					
Background information, incl. Socioeconomic status (SES)	X			X	
Depressive symptoms (EPDS and GMDS)					X

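### Categorical secondary outcomes go to multinomial logistic regression, yet the one listed outcome likely to be analysed that way, the information ratings, is ordered and has a directional aim

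*Protocol article*

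**What the plan says.** In the protocol article, Statistical methods assigns models by outcome type: "Binary and categorical outcomes will be analysed with mixed logistic and multinomial logistic regressions, respectively", "and continuous outcomes with mixed linear regression analyses". It does not list which outcomes count as categorical, and it names no model for ordered categories.

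Under Secondary study outcomes, the information outcome at 11 months is a graded rating, topic by topic: "Parents are asked to what degree they have been informed about each of the following topics by their health visitor". Of six topics, four matter for the trial: "we are interested in whether parents have received more information about the last four topics". No total score is described. The response options are in Additional file 2, which is not shown here. Purpose of the study states the aim with a direction: "Increased information about infant socioemotional development (secondary outcome".

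For the ASQ:SE-2, the same section defines a score, "Items are summed to a total score with higher values reflecting less optimal socioemotional development", and adds that cutoffs exist to judge "whether the child’s socioemotional development appears to be on schedule, in the monitor zone, or in need for further evaluation". It does not make those three zones an endpoint.

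**The concern.** As described in the text, the secondary outcomes are summed scores (PRFQ subscales, PSI-4-SF, ASQ:SE-2, ADBB), a proportion (mind-mindedness), minutes or counts per day (media use), and the information ratings. None is described as an unordered category. The multinomial clause therefore either applies to ordered data or has nothing to apply to, and the information ratings are the natural candidate.

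Applied to them, the model gives K-1 odds ratios per item and a group test on K-1 degrees of freedom that responds to any difference in the distribution, whether or not it is an increase. A cumulative-logit model gives one odds ratio that answers the stated question. At stake is a useful process check: this outcome is the parents' own report of whether health visitors conveyed the socioemotional content, and it would help to interpret a null result on PSOC.

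**Working it through.** **The plan's own figures.** The article gives no power or sample size for any categorical outcome. Its Sample size section gives 690 analysed participants for d = 0.2 on the primary outcome, and 690/(1 - 0.25) = 920 recruited, which reproduces. For reference, an unadjusted two-sided comparison of means with 345 per group and d = 0.2 has 74.8% power.

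**Inputs**
- From the article: 690 analysed (taken as 345 per group), shift 0.2 SD, 5% two-sided.
- Assumed: four or five response levels, equally filled under CAU; a normal latent variable shifted by 0.2 SD under UYB; no clustering or covariates in either test.

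**Step 1: category shares under UYB.** Each CAU cut-point c becomes c - 0.2 on the normal scale.
- Five levels: 20% each becomes about 14.9, 17.6, 19.6, 21.8 and 26.1%.
- Four levels: 25% each becomes about 19.1, 23.0, 26.2 and 31.8%.

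**Step 2: ordinal test (1 df).** This is the Wilcoxon test, the score test of the proportional-odds model. Z = (difference in mean ridit) / sqrt(v × 2/n), with v = (1 - Σp̄³)/12, where p̄ is the average share of a category over the two groups.
- Five levels: v = 0.0799, so Z = 0.0531/0.0215 = 2.47 and power is about 69%.
- Four levels: v = 0.0780, so Z = 0.0515/0.0213 = 2.42 and power is about 68%.

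**Step 3: multinomial group test (K-1 df).** The noncentrality is 2n × Σ[p0 ln(p0/p̄) + p1 ln(p1/p̄)].
- Five levels: 6.16 on 4 df, power about 48%.
- Four levels: 5.91 on 3 df, power about 51%.

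**Step 4: simulation, 20,000 trials per scenario.** Ordinal versus multinomial power:

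| Assumed scale and effect | Ordinal | Multinomial |
|---|---|---|
| Five even levels, shift 0.2 SD | 69.2% | 48.3% |
| Four even levels, shift 0.2 SD | 68.0% | 51.6% |
| Five levels (10/20/30/25/15%), common odds ratio 1.5 | 84.8% | 65.6% |
| Four levels (10/25/40/25%), common odds ratio 1.5 | 82.7% | 67.7% |

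**Step 5: general size.** Suppose the 1-df ordinal test has exactly 80% power, a noncentrality of (1.960 + 0.842)² = 7.85. The multinomial test then has 64.5% (K = 4) or 59.5% (K = 5). To regain 80% it needs 1.39 or 1.52 times as many participants.

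**Step 6: validity and direction.** With no group difference (odds ratio 1), both tests reject in 4.8 to 5.5% of trials, so type I error is kept. With a pure spread to both extremes and no net shift (10/20/40/20/10% against 15/20/30/20/15%), the multinomial test rejects in 80% of trials and the ordinal test in 5%. A significant multinomial test therefore need not mean that information increased.

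**The case against.** The strongest reply is that the article never says the information ratings will be analysed as categories. Statistical methods opens its treatment of secondary outcomes by extending the primary linear mixed model to them, and other Likert-type scales in the article are summed. Summed or numeric information items would never reach the multinomial model, and assigning each outcome to a model is often left to a statistical analysis plan. This stands as a condition on the point: the loss arises only if the ratings are treated as categories. It does not remove the point, because the choice of a multinomial model for categorical outcomes is stated in the article, and no total is described for this outcome as it is for the others.

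The reply also holds that the multinomial model is valid, avoids the proportional-odds assumption and can be the more powerful test when the shift is not uniform. All of that is right.

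Three stronger readings are tempting and are not supported:
- **That the ASQ:SE-2 zones will be tested with this model.** The article makes the summed score the measure, which falls under linear regression, and says only that cutoffs are available.
- **That the multinomial model cannot address direction.** Its category-specific odds ratios have signs. It is the overall test that is non-directional, and no single directional contrast is fixed.
- **That the loss grows after the Bonferroni-Holm adjustment.** Starting from the simulated ordinal power and using the approximation of Step 5, the gap for five levels is about 22 percentage points at 0.05 and 18 at 0.005; for four levels it is 17 and 14. It rises by less than one point at 0.025. Only the relative loss grows.

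**Conclusion.** The point holds in conditional form. The only model the article names for multi-category outcomes ignores order, while the one listed outcome likely to need such a model is ordered and has a directional aim. If the four information ratings are analysed as categories, the test remains valid, but power falls from about 68 to 69% to about 48 to 52%, a loss of roughly 16 to 21 percentage points.

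That size rests on four or five response levels, evenly filled categories, a roughly uniform shift of 0.2 SD borrowed from the primary outcome's sample-size calculation, 345 per group, and no clustering or covariates. A different scale or a non-uniform effect would change it. This is a matter of efficiency and interpretation for one secondary outcome. The primary PSOC analysis and the 690/920 figures are not touched.

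**What to change.** In Statistical methods, specify a mixed cumulative-logit (ordinal) model for ordered categorical outcomes. Name the information ratings, and the ASQ:SE-2 zones only if they are to be analysed. Use the same covariates and health-visitor random effect as in the other models and report one odds ratio per outcome. Keep the multinomial fit as a check of proportional odds. If the information items are instead to be summed or treated as numeric, say so; the linear model then applies and the issue does not arise.

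The cost is a sentence or two of wording, with no change to data collection. The one downside is that the proportional-odds assumption has to be checked and reported.
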